### Sample size

The VPDD from 2013-2019 has recorded an average of 147 CNVs (85 VUS, 62 pCNVs) each year. Our total potential CNV cohort for the proposed 7-year study period will be approximately 1029.

We expect losses of potential recruits due to failed contact tracing, language ineligibility, perinatal loss, and refusal of consent, and therefore conservatively estimate a final sample size of 354 women for the CNV cohort. This is based on 45% recruitment of women with fetal VUS (n=267), and 20% recruitment rate for pathogenic CNVs (n=87). This is in line with participation rates in the NICHD microarray cohort where they achieved 41%, 56% and 70% participation rates for those with pathogenic, VUS or benign/normal CMA results respectively [16]. There are 7155 potential eligible controls in the study period. We will require 5% of women with normal CMA results to be recruited to form the control cohort (n=358).

### Recruitment of potential participants

This will involve a multi-step pre-screening stage to maintain patient privacy and minimize the chance of approaching ineligible women to participate (Fig. 1).

**Fig. 1 Fig1:**
[figure not shown]
Recruitment strategy. Abbreviations: BHH (Box Hill Hospital); CMA (chromosomal microarray analysis); ID (Identifier); MCRI (Murdoch Children’s Research Institute); MHW (Mercy Hospital for Women); MMC (Monash Medical Centre); PALM (PrenatAL Microarray); PI (Principle Investigator); PICF (Participant Information Consent Form); RWH (Royal Women’s Hospital); VPDC (Victorian Perinatal Data Collection); VPDD (Victorian Prenatal Diagnosis Data collection)

**Fig. 2 Fig2:**
[figure not shown]
Participant flowchart including estimated recruitment rates by CNV subgroup (pathogenic CNV or variant of uncertain significance). Abbreviations: ASQ:SE-2 (Ages and Stages Questionnaire: Social-Emotional-2); ASQ-3 (Ages and Stages Questionnaire, third edition); BITSEA (Brief Infant-Toddler Social and Emotional Assessment); BRIEF (Behaviour Rating Inventory of Executive Function); BRIEF-P (Behaviour Rating Inventory of Executive Function – Preschool version); pCNVs (pathogenic copy number variant); MPAS (Maternal Postnatal Attachment Questionnaire); VABS (Vineland-II Adaptive Behaviour Scale); VUS (variants uncertain/unknown significance); WPPSI-IV (Wechsler Preschool and Primary Scale of Intelligence IV)

### Pre-screening

The aim of the pre-screening stage is to accurately identify potential eligible participants, and to avoid contacting women who may have experienced a perinatal loss in the relevant pregnancy. For this reason, the involvement of the clinical referrer in the recruitment process is considered essential.

Pre-screening will include the following:

(i) Pre-screening stage 1. Audit of prenatal CMA results at the VPDD to identify potential participants based on prenatal diagnosis results. This will be performed by the study team at the MCRI who manage the VPDD. A list containing all records with a CNV detected on CMA during the study period will be generated and categorized into pCNV or VUS groups. A list of non-CNV records, where there is no fetal structural abnormality, will also be created as the control cohort. Each record will have the limited individual identifiers from the contributing cytogenetic laboratories, available under the existing VPDD ethics protocol (i.e., first three letters of maternal surname and first name, date of testing, type of test, date of birth).

(ii) Pre-screening stage 2. This list of potential participants from the VPDD with the limited identifiers will be sent in a secure file to the respective laboratories that performed the CMA testing using Research Electronic Data Capture (REDCap), a secure web application specifically designed to support online and offline data capture for research studies [17, 18].

(iii) Pre-screening Stage 3. Individual lists of potential participants for each clinical practice location will be generated by the participating laboratories. The vast majority will be captured through the five public hospital fetal medicine units: The Royal Women’s Hospital, The Mercy Hospital for Women, Monash Medical Centre, Sunshine Hospital and Box Hill Hospital. Approximately 20% will be from private obstetricians and regional referrals.

(iv) Pre-screening Stage 4. Examination of health records for exclusion criteria by the clinical referrers. The protocol will vary depending on whether the referral came from a public hospital or private practice.

#### Public hospital fetal medicine units

The lead prenatal genetic clinician and/or the senior genetic counsellor at each of the five fetal medicine units will act as site Principal Investigator (PI) (see acknowledgements for full list of site PIs and associate investigators) and oversee any data collection. The medical records of potential participants sent as a listing from the laboratory will be examined by the site PI to identify those that are eligible. They will also collect deidentified data on ineligible individuals to determine the attrition rate and frequency of factors that lead to ineligibility (Table 1).

**Table 1 Tab1:** Data elements collected on ineligible individuals

Pregnancy results in perinatal loss (miscarriage, stillbirth, neonatal death, or termination of pregnancy)	
Interpreter required (non-English speaking); language	
Woman unable to given informed consent for medical care	
Year of prenatal diagnosis	
Multiple pregnancy	
Relocation interstate during pregnancy	
Mother not intended to be primary care-giver of child	
Unable to be assessed (missing data)	

For those women that did not give birth in the fetal medicine unit where the prenatal diagnosis took place (e.g., women from regional Victoria referred to tertiary units for prenatal diagnosis), the planned hospital of birth and the clinical referrer will be recorded by the PI. A letter or email from study team will be sent to the original clinical referrer to ask if their participant meets the eligibility requirements for the study.

#### Private practice referrers

The laboratory will send either a letter or email regarding potentially eligible recruit(s) to the private obstetrician who referred their patient(s) for prenatal diagnosis. The private practice clinician will be asked to perform an assessment of their patient’s eligibility.

### Recruitment and enrolment

All women who meet the eligibility criteria will be sent an invitation letter and a Participant Information & Consent Form (PICF) by post +/- email (if available) from the clinical referral source. All eligible women in the CNV group will be invited. Based on the above estimated participation rates, we will initially invite 716 women in the non-CNV group, with further invitations to be sent if we do not achieve our target sample size in the control group (Fig. 2). Those who wish to participate will be asked to complete an online consent form in REDCap, accessed via a QR code in the invitation letter. Alternatively, a hard copy consent from can be completed and sent to the Murdoch Children’s Research Institute (MCRI) either via email or in an enclosed postage-paid envelope. The MCRI study coordinator will be the primary contact for all women who are considering participation.

A single reminder letter will be sent three weeks after the initial invitation. If there is no response after this, no further contact will be attempted.

### Ineligible and non-responding individuals

De-identified data will be maintained on all individuals who are deemed ineligible during the pre-screening stage in order to ascertain the representativeness of our cohort and its generalizability to our prenatal diagnosis population. Those women who were invited but did not provide consent to the MCRI team will be considered “non-responders”. We will not collect individual identifiers of these women.

### Screening and baseline health assessment

Baseline variables will be collected directly from the woman by telephone, online survey, or hardcopy postage according to the participant’s preference.

These will include:
A review of her history to confirm eligibility and willingness to perform the study procedures (parent-completed questionnaires +/- child study visits)Baseline demographic and health assessment data
Maternal and household informationPregnancy and newborn outcomesMaternal state and trait anxietyMaternal health literacyHealth care utilizationMissing baseline pregnancy outcomes may be collected from health service medical records and/or via linkage to the Victorian Perinatal Data Collection. Women will be asked to provide specific optional consent for data linkage to the Victorian Perinatal Data Collection (VPDC) [19].Women will be asked to provide specific optional consent for access to the School Entrant Health Questionnaire (SEHQ) at the time of consenting to participate in the PALM study. This is a parent report instrument that records parent’s concerns and observations about their child’s health and wellbeing as the child begins primary school in Victoria. A separate application to the Department of Education will be made for access to these data on those participants providing specific consent.

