## Methods/Design

### Aims

The PALM cohort study will establish and follow-up a cohort of mother-child pairs who had a prenatal diagnosis of a CNV from 2013-2019 (inclusive) in the Australian state of Victoria. Victoria has approximately 78,000 births per year and a median maternal age of 31.5 years [13]. Approximately 2-3% of all pregnant women undergo prenatal diagnosis per year [14].

The study aims are to:
Compare the developmental, social-emotional and health status of children with a prenatal diagnosis of a prenatal CNV with those children with no CNV detected on CMA.Measure the impact of a prenatal diagnosis of a CNV on maternal perceptions of child health, behavior, and development.Determine the proportion of CNV ascertained prenatally that are reclassified from unknown or uncertain to benign or pathogenic after two or more years using contemporaneous curation resources.

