Quantitative survey	‘Younger cohort’ children who are 12-30 months old at the time of enrolment	Ages and Stages Questionnaire-3	Parent	Online or hard copy. 20-30 minutes.
		Ages and Stages Questionnaire Social Emotional-2	Parent	
Quantitative survey	‘Older cohort’ children who are 2 years 7 months to 7 years 7 months at the time of enrolment	The Vineland-II Adaptive Behavior Scale (VABS)	Parent	Online or hard copy. 20-60 minutes
Psychologist assessment		Wechsler Preschool and Primary Scale of Intelligence IV (WPPSI-IV)	Psychologist	In person. 20-60 minutes
Clinical assessment		Clinical assessment by study pediatrician: measurements of height, weight, and head circumference; history and physical examination	Paediatrician	In person. 20-60 minutes
**Outcome 3:** The frequency of copy number variants that have a change in classification after reanalysis after ≥2 years will be presented in a descriptive analysis. For the participants in the reanalysis group, an additional letter will be sent to them with the results of the updated analysis.				
Clinical standard laboratory software and databases in use during 2021-2022	Children who were prenatally diagnosed with a copy number variant of uncertain or unknown significance	Affymetrix Chromosome Analysis Suite (ChAS) software	Cytogenetics Laboratory	n/a
		DatabasE of Chromosomal Imbalance and Phenotype in Humans using Emsembl Resources (DECIPHER)	Cytogenetics Laboratory	
		International Standards for Cytogenomic Arrays (ISCA) database	Cytogenetics Laboratory	
		Online Mendelian Inheritance in Man (OMIM)	Cytogenetics Laboratory	

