#### For the 12–24-month-old group, the ASQ-3 and ASQ:SE-2 scores are the primary outcomes

Scores for individual items are summed to give an overall continuous score for each of the domains in the ASQ-3 and ASQ:SE-2. In addition to using scores as continuous outcomes, we will categorize the scores according to the recommended scores for typical development, need for monitoring, and need for further assessment. We will collapse these three categories into a binary variable (those with typical development vs those with a need for monitoring or further assessment [i.e., potential atypical or delayed development]). The differences in those with typical and ‘atypical’ scores will be compared among the CNV subgroup using chi-squared test for proportions or Fisher’s exact test as appropriate.

#### Objective 2

The primary outcome will be the BITSEA score. We will analyze the data according to the subgroup of CNV result (pCNV, VUS) compared with controls, stratified by age. The secondary outcomes will be the Maternal Postnatal Attachment Questionnaire (MPAS), Vulnerable Child Scale (VCS), Profile of Mood States (POMS), and the Parent Sense of Competence Scale (PSOC). For the secondary outcomes, we will compare group differences in responses using mixed effect regression models. We will report mean values for the parent report of child behavior, parenting competence, attachment, perceived child vulnerability and parent mood. Parent gender, country of birth, education, employment status, and child sex will be adjusted as covariates.

#### Objective 3

We will compare the classifications given at the time of issue of the prenatal report and the current classifications in 2020-21 according to the issuing laboratory’s protocols. The proportion of pCNVs, VUS and benign variants will be compared between the prenatal and 2-year postnatal classifications using chi-squared test for proportions.

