### Women’s experience of prenatal VUS

While most children with VUS are expected to have normal outcomes, the possibility of an increased risk of developmental disorder can result in parental anxiety, termination of healthy pregnancies, “hypervigilant” parenting styles, and increased utilization of medical services [36]. A prenatal diagnosis of a VUS may also alter early parental perceptions of the competency of the child [16]. Our study will be able to determine whether there are any such ‘harms’ associated with the disclosure of VUS, and enable us to develop strategies to mitigate these negative effects.

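### Objective 2 adjusts its secondary outcomes for employment status, which as described is collected one to eight years after the CNV result and may be a consequence of it

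*Protocol article*

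**What the plan says.** The Aims section of the protocol article words the second aim as an effect: "Measure the impact of a prenatal diagnosis of a CNV on maternal perceptions of child health, behavior, and development". It does not say that an effect net of employment is meant.

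For Objective 2, the statistical section makes BITSEA the primary outcome and MPAS, VCS, POMS and PSOC the secondary ones. It continues: "For the secondary outcomes, we will compare group differences in responses using mixed effect regression models". After a sentence on reporting means, it fixes the adjustment set: "Parent gender, country of birth, education, employment status, and child sex will be adjusted as covariates".

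The section Screening and baseline health assessment gives the source of baseline data: "Baseline variables will be collected directly from the woman by telephone, online survey, or hardcopy postage". Its list includes a broad item on the mother and household but does not name employment or give a reference date for it. Medical records and perinatal data linkage are described only for filling in missing pregnancy outcomes.

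Table 2 gives the ages at study entry: "Younger cohort’ children who are 12-30 months old at the time of enrolment" and "Older cohort’ children who are 2 years 7 months to 7 years 7 months at the time of enrolment". Under Inclusion criteria, the exposure is a microarray result reported during a pregnancy in 2013 to 2019.

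**The concern.** Baseline here means entry to the study, not the time before exposure. A mother may have left or reduced paid work because of the result, closer watching of the child, extra appointments or the child's needs. The Discussion subsection on women's experience of prenatal VUS expects anxiety, hypervigilant parenting and "increased utilization of medical services", which makes such a path plausible, although it does not mention work. Employment is also plausibly related to mood and sense of competence.

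If both links exist, current employment lies between the exposure and the outcome. Adjusting for it takes out the part of the impact that runs through employment. It can also introduce bias through unmeasured causes that employment and mood share. The estimate would then answer a different question from the one in aim 2. At stake is the study's stated purpose of finding out whether disclosing a VUS does harm.

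The other listed covariates raise this less. Country of birth and child sex cannot be changed by the result, and education is comparatively stable.

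**Working it through.** The plan gives no figure on this point, so there is none to reproduce. Two things can be checked.

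**1. Time from result to collection.**
- Child's age at entry: 1 year to 7 years 7 months (7.58 years), from Table 2.
- Result to birth: assumed 4 to 28 weeks; the article gives no figure. At 52.18 weeks per year this is 0.08 to 0.54 years.
- Youngest child: 1 + 0.08 = 1.08 to 1 + 0.54 = 1.54 years.
- Oldest child: 7.58 + 0.08 = 7.66 to 7.58 + 0.54 = 8.12 years.

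The item is therefore collected about one to eight years after the result.

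**2. What adjustment could remove.** In a linear model with no unmeasured shared cause of employment and score, the part removed is d × b. Here d is the difference in employment rate caused by the result, and b is the effect of employment on the score in SD. The share removed is d × b / T, where T is the total effect. All three values are assumptions. With T = 0.2 SD:

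| Shift in employment, d | b = 0.1 SD | b = 0.2 SD | b = 0.4 SD |
|---|---|---|---|
| 0 points | 0% | 0% | 0% |
| 5 points | 2.5% | 5% | 10% |
| 10 points | 5% | 10% | 20% |
| 20 points | 10% | 20% | 40% |

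Example: 0.10 × 0.4 = 0.04 SD, and 0.04 / 0.2 = 20%. A simulation of 400,000 records checked this cell, with employment of 70% v 60%, a direct effect of 0.16 SD and an employment effect of 0.4 SD. The group difference was 0.20 SD unadjusted and 0.16 SD adjusted.

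The table takes employment to improve the score. If non-employment improved a scale, the sign of d × b would reverse and adjustment would enlarge the adverse contrast.

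**3. Scale against precision.** With the planned 267 VUS participants and 358 controls, the standard error of a simple mean difference is √(1/267 + 1/358) = 0.081 SD. For 87 pCNV participants and 358 controls it is √(1/87 + 1/358) = 0.120 SD. The amounts removed run from 0.05 × 0.1 = 0.005 SD to 0.20 × 0.4 = 0.08 SD, so the largest is about one standard error of the VUS comparison.

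**The case against.** The strongest objection is that employment may also stand for socioeconomic position before the result, which is a genuine confounder. Frequency matching covers fetal sex, trimester, maternal age group and calendar year, but nothing socioeconomic. Expected participation also differs: 45% for VUS, 20% for pCNVs, and 358 of 716 initial invitations (50%) for controls. Simply dropping employment could leave confounding or selection bias. This stands, and it rules out deletion as the remedy. It does not defend using a value that may date from after the result.

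Second, the questionnaire is not shown. Employment is not named among the baseline items, and the same survey asks about the past pregnancy, so the item could already refer to that time. This also stands, and the point is therefore conditional on the item recording current employment.

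Third, a reader might infer that the model does remove part of the impact and so favours a false finding of no harm. The article does not support that. It nowhere says that the result changes employment or that employment changes these scores. The direction need not be towards zero on every scale: for attachment, more time at home could work the other way.

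Fourth, larger losses can be produced by assumption. With a direct effect of 0.15 SD and a 15-point shift, employment effects of 0.3 and 0.5 SD give 0.045 / 0.195 = 23% and 0.075 / 0.225 = 33%. Nothing in the article supports a shift of that size. VUS make up 267 of the planned 354 CNV participants (75%), and the Discussion expects most children with VUS to have normal outcomes.

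Finally, the covariate sentence follows the models for the secondary outcomes. Extending the point to BITSEA, the primary outcome of Objective 2, would go beyond the text. The promised means, if unadjusted, would also let readers see the contrast without employment.

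**Conclusion.** The point holds in conditional form. The plan fixes employment status as a covariate for an aim worded as total impact, and the only described source is contact with the mother at least a year after the result. If the item records current employment, adjusting for it may bias the MPAS, VCS, POMS and PSOC comparisons. Neither the size nor the direction can be settled from the article. The illustrative range is 0 to 40% of a 0.2 SD effect, with small losses for small shifts in employment and none if the result does not affect it. The conclusion also rests on reading aim 2 as a total effect, which is its natural sense. The correction is worth making because it is cheap and keeps the socioeconomic control that the covariate was presumably meant to give.

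**What to change.** - Define the covariate as the mother's employment during the index pregnancy, before the result. If the survey does not already ask this, add one item.
- Keep education and country of birth, so that prior socioeconomic position stays controlled.
- Take current employment out of the main Objective 2 models. Report it in a sensitivity model labelled as adjusting for a variable measured after the result.
- If the survey is already complete and holds only current employment, report the models with and without it. Interpret the difference with both explanations in view: employment as a consequence of the result, and employment as a marker of earlier socioeconomic position.

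The cost is at most one survey item, one redefined covariate and one extra model. The main downside is recall, which for the oldest children reaches back about eight years. The fallback needs no new data, but it cannot separate the two explanations.

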### Data collection

Child outcome data will be collected via parent-completed quantitative surveys using validated measures and through psychologist and/or pediatrician assessment. See Table 2 for an overview of study instruments used for each outcome measure. The study data will be collected in 5 main forms.
Parent-completed questionnaires – off-site, in parent’s own timeVineland Adaptive Behavior scale (VABS) – telephone interview with mother conducted by a study psychologistWPPSI-IV – child assessment conducted on-site by a study psychologist at the Melbourne Children’s Trials Centre, Parkville, MelbourneClinical assessment by study pediatrician – conducted on-site at the same visit as the WPPSI-IV wherever practicable.Laboratory reanalysis of the prenatal CNV result - no interview or participant attendance required.

**Table 2 Tab2:** Overview of study instruments used in the PALM study for children aged 12 months to 7 years

Data collection method	Time point	Instrument	Completed by	Delivery and time
**Outcome 1:** To compare the developmental, social-emotional and health status of children with a prenatal diagnosis of a prenatal copy number variant with those children with no copy number variant detected on chromosomal microarray.				
Quantitative survey	Children aged 12 months or older.	Brief Infant-Toddler Social and Emotional Assessment (BITSEA) [20]	Parent	Online or hard copy. 30-40 minutes total
		Strengths and Difficulties Questionnaire (SDQ) [21]	Parent	
		Maternal Postnatal Attachment Questionnaire (MPAS) [22]	Parent	
		Vulnerable Child Scale (VCS) [23]	Parent	
		Profile of Mood States (POMS) [24]	Parent	
		Parent Sense of Competence Scale (PSOC) [25]	Parent	
		Golombok Rust Inventory of Marital State (GRIMS) [26]	Parent	
		Disclosure of Results to Others [27]	Parent	
		Secrecy about Results [28]	Parent	
		Decision Satisfaction Scale [29, 30]	Parent	
		Revised Scale of Ambiguity Tolerance [31]	Parent	
		Genetic essentialism, general understanding of genetics and accuracy of understanding of results [32, 33]	Parent	
		Patient Health Questionnaire depression scale (PHQ-8)	Parent	
		Children with Special Health Care Needs (CSHCN) screener [34]	Parent	
**Outcome 2:** To measure the impact of a prenatal diagnosis of a copy number variant on maternal perceptions of their child.				
Quantitative survey	‘Younger cohort’ children who are 12-30 months old at the time of enrolment	Ages and Stages Questionnaire-3	Parent	Online or hard copy. 20-30 minutes.
		Ages and Stages Questionnaire Social Emotional-2	Parent	
Quantitative survey	‘Older cohort’ children who are 2 years 7 months to 7 years 7 months at the time of enrolment	The Vineland-II Adaptive Behavior Scale (VABS)	Parent	Online or hard copy. 20-60 minutes
Psychologist assessment		Wechsler Preschool and Primary Scale of Intelligence IV (WPPSI-IV)	Psychologist	In person. 20-60 minutes
Clinical assessment		Clinical assessment by study pediatrician: measurements of height, weight, and head circumference; history and physical examination	Paediatrician	In person. 20-60 minutes
**Outcome 3:** The frequency of copy number variants that have a change in classification after reanalysis after ≥2 years will be presented in a descriptive analysis. For the participants in the reanalysis group, an additional letter will be sent to them with the results of the updated analysis.				
Clinical standard laboratory software and databases in use during 2021-2022	Children who were prenatally diagnosed with a copy number variant of uncertain or unknown significance	Affymetrix Chromosome Analysis Suite (ChAS) software	Cytogenetics Laboratory	n/a
		DatabasE of Chromosomal Imbalance and Phenotype in Humans using Emsembl Resources (DECIPHER)	Cytogenetics Laboratory	
		International Standards for Cytogenomic Arrays (ISCA) database	Cytogenetics Laboratory	
		Online Mendelian Inheritance in Man (OMIM)	Cytogenetics Laboratory	

